# Testing the effectiveness and implementation of a brief version of the Common Elements Treatment Approach (CETA) in Ukraine: a study protocol for a randomized controlled trial

**DOI:** 10.1186/s13063-018-2752-y

**Published:** 2018-08-03

**Keywords:** Global mental health, Transdiagnostic, Depression, Veterans, Internally displaced persons, Trauma, Cognitive-behavioral therapy, Implementation research

## Abstract

**Background:**

Mental illness is a major public health concern. Despite progress understanding which treatments work, a significant treatment gap remains. An ongoing concern is treatment length. Modular, flexible, transdiagnostic approaches have been offered as one solution to scalability challenges. The Common Elements Treatment Approach (CETA) is one such approach and offers the ability to treat a wide range of common mental health problems. CETA is supported by two randomized trials from low- and middle-income countries showing strong effectiveness and implementation outcomes.

**Methods/design:**

This trial evaluates the effectiveness and implementation of two versions of CETA using a non-inferiority design to test two primary hypotheses: (1) a brief five-session version of CETA (Brief CETA) will provide similar effectiveness for reducing the severity of common mental health problems such as depression, post-traumatic stress, impaired functioning, anxiety, and substance use problems compared with the standard 8–12-session version of CETA (Standard CETA); and (2) both Brief and Standard CETA will have superior impact on the outcomes compared to a wait-list control condition. For both hypotheses, the main effect will be assessed using longitudinal data and mixed-effects regression models over a 6-month period post baseline. A secondary aim includes exploration of implementation factors. Additional planned analyses will include exploration of: moderators of treatment impact by disorder severity and comorbidity; the impact of individual therapeutic components; and trends in symptom change between end of treatment and 6-month assessment for all participants.

**Discussion:**

This trial is the first rigorous study comparing a standard-length (8–12 sessions) modular, flexible, transdiagnostic, cognitive-behavioral approach to a shortened version of the approach (five sessions). Brief CETA entails “front-loading” with elements that research suggests are strong mechanisms of change. The study design will allow us to draw conclusions about the effects of both Brief and Standard CETA as well as which elements are integral to their mechanisms of action, informing future implementation and fidelity efforts. The results from this trial will inform future dissemination, implementation and scale-up of CETA in Ukraine and contribute to our understanding of the effects of modular, flexible, transdiagnostic approaches in similar contexts.

**Trial registration:**

ClinicalTrials.gov, ID: NCT03058302 (U.S. National Library of Medicine). Registered on 20 February 2017.

**Electronic supplementary material:**

The online version of this article (10.1186/s13063-018-2752-y) contains supplementary material, which is available to authorized users.

## Background

Mental, neurological, and substance use disorders account for 10.4% of the global burden of disease [1]. The field of global mental health has made significant advances over the past decade in understanding the effectiveness of various evidence-based mental health treatments in low- and middle-income countries (LMIC) [2–10]. Despite this progress, the availability of such evidence-based treatments is limited by multiple challenges around buy-in, scale-up, and sustainability. Research shows that most individuals with mental health needs do not receive care - creating a substantial mental health “treatment gap” [11–13].

One possible strategy for addressing the challenge of scale-up is utilizing a transdiagnostic approach, in which providers receive training in *one* approach that can address multiple common mental health problems and comorbidity [14]. The use of transdiagnostic approaches may prevent the need to train providers in multiple focal treatments, which creates challenges for scale-up in terms of time and cost, and has limited ability to address comorbidities. Various transdiagnostic models, some modular, initially were developed and tested in high-income settings, and have demonstrated effectiveness and provider appeal [15–18]. The term transdiagnostic is widely used with varying underlying conceptualizations. In their conceptualization, Sauer-Zavala and colleagues [19] describe three approaches: (1) a *universally applied principles approach*, which is based on a school of thought (e.g., psychodynamic, cognitive-behavioral, humanistic) that is then applied to multiple disorders regardless of symptom presentation; (2) a *modular or common-elements approach*, which involves using components or elements of existing evidence-based treatments that can be delivered in different orders and combinations to address symptom presentation and wide-ranging comorbidities; and (3) a *shared mechanism approach*, which is informed by theory and targets underlying processes of certain disorders. Other potential differences across transdiagnostic treatments, regardless of how they are conceptualized, include more structural aspects such as dosage or intensity (e.g., number of sessions), decomposability or modularity (the degree to which elements are mostly independent of one another), flexibility, linearity, and whether or not they are multi-problem [20].

Building on growing empirical support for transdiagnostic treatments and their potential promise for efficiency, our research team developed The Common Elements Treatment Approach (CETA) [21], a modular, flexible, transdiagnostic approach specifically for LMIC, in which task-sharing is used, and providers often have minimal or no formal mental health training. CETA was modeled on a treatment developed by Drs. John Weisz and Bruce Chorpita [18, 22–25], specifically to be a modular, flexible, transdiagnostic approach as that was believed to have the most potential to address implementation and scale-up barriers in LMIC. Such transdiagnostic models could address a wide range of comorbid problems across the life span (reducing the number of treatments needed), with the ability to only deliver the dosage needed (potentially reducing cost and resources). The goal in adapting an existing intervention—versus just using the existing intervention—was to create a more simplified approach that had a limited number of elements, simple language, a short manual with practical step-sheets, and decision rules giving providers and their supervisors flexible choices in element selection, sequencing, and dose. The decision rules help the provider use the client’s initial assessment (e.g., primary presenting problem; comorbidity) and ongoing presentation (e.g., symptom changes during treatment) to plan and adjust treatment as needed [21]. Our team has evaluated CETA effectiveness with adults in Iraq and Thailand, demonstrating that providers with minimal or no formal mental health training could provide CETA with fidelity and achieve positive outcomes with their clients (large effect sizes across outcomes) [2, 26].

Although the field of global mental health has a number of evidence-based mental health treatments with evidence of effectiveness, treatment duration is often cited as a significant barrier to scale-up and reduction of the treatment gap as the longer the treatment, the more staff and resources are needed, and the potential for dropout increases. Previous studies of cognitive-behavioral therapy (CBT)-based interventions, interpersonal psychotherapy, and CETA in LMIC have been tested with treatment durations of approximately 8–12 1 hour sessions [3, 7, 9, 26–28]. Scale-up challenges have led to a push to develop intervention models that are even briefer, particularly for highly mobile populations, such as trauma-affected groups or displaced persons [29]. A modular, flexible, transdiagnostic model provides an opportunity to decrease the length of treatment based on need (e.g., utilizing fewer elements), but still catering to the comorbid problems experienced by any population or individual.

There may be different methods to reducing the length of treatments. One approach to developing shorter interventions is to focus on elements or skills that may be easier to learn. Another approach is to identify treatment elements that seem to be essential, and, when treatments have been subjected to dismantling studies—account for greater variance in client outcomes. For example, although cognitive elements may be more challenging for lay providers and/or clients to understand and master, cognitive elements are also among those most frequently used in many evidence-based treatments for common mental health problems. Research suggests that cognitive interventions can be learned by lay counselors when provided with coaching and supervision [3, 9, 26, 28], and given their broad use in a number of evidence-based protocols may represent an important mechanism of action. Interventions using cognitive skills have been tested in LMIC and have shown evidence of effectiveness, often with large effect sizes. For example, in a study focused on survivors of sexual violence in Democratic Republic of Congo, Bass and colleagues [3] evaluated Cognitive Processing Therapy – Cognitive Therapy, which is an intervention that focuses primarily on cognitive elements. Effect sizes were greater than 1.0 for post-traumatic stress disorder (PTSD) and combined depression and anxiety. Trials in LMIC that used evidence-based treatments, including cognitive elements, with youth participants have also been shown to be effective, even when delivered by lay providers.

To explore whether the CETA approach could be provided in fewer sessions and with fewer elements, yet retain effectiveness, we designed a five-session intervention that is “front-loaded” with the elements that are most commonly used in evidence-based practices per distillation work [30], the empirical academic literature, and research studies conducted in LMIC with lay providers. Our working hypothesis is that these elements are the “strongest” mechanisms of action and, given past research in LMIC, are feasible elements for lay providers to deliver effectively. The study design is a non-inferiority trial and a trial of effectiveness by comparing a five-session, “front-loaded,” Brief version of CETA to Standard CETA (8–12 sessions) and both versions to a wait-list control.

## Methods/design

### Study aims

This trial is designed to test two primary study hypotheses: (1) that a brief five-session version of CETA (Brief CETA) will provide similar effectiveness for reducing the severity of depression and post-traumatic stress (PTS) symptoms and improving daily functioning compared with the standard 8–12-session version of CETA (Standard CETA) and (2) that both Brief and Standard CETA will provide substantial impact for these same outcomes compared to a wait-list control condition. For both hypotheses, the main effect will be assessed 6 months post baseline.

Secondary aims include an exploration of implementation factors, including treatment fidelity, barriers and facilitators to the intervention implementation at the client and provider levels, and an exploration of unexpected additional effects of the program, both positive and negative. Planned secondary analyses include exploration of moderators of treatment impact by severity of disorders and comorbidity, examination of the impact of individual therapeutic components, and trends in symptom change between end of treatment and 6-month assessment for those in either Brief or Standard CETA.

### Study context

This study is being conducted in Ukraine. Starting at the end of 2013 through early 2014, Ukraine experienced a period of rapidly increasing and widespread political discontent. In March 2014, Russia annexed Crimea in Eastern Ukraine, which began a series of violent events that continue today between pro-Russian separatists (supported by Russia) and Ukrainians supportive of the new government. These events have resulted in significant social and economic disruption and dislocation, with many individuals and families experiencing significant trauma and violence. This has included large numbers of individuals from across the country being conscripted into military service, hundreds of thousands of people being displaced from the eastern regions of Donetsk and Luhansk (the Donbass) and Crimea, and host communities being impacted by the influx of internally displaced persons. According to the Internal Displacement Monitoring Center [31], there are nearly 1.7 million internally displaced persons in Ukraine as of August 2015 with likely more who are displaced but not officially registered.

Between February and March of 2016, we conducted a brief qualitative study with internally displaced persons from the Donbass and military veterans living in two eastern oblasts, or regions, of Ukraine: Zaporizhia and Kharkiv. The aim of this formative study was to inform the adaptation of the CETA intervention to the Ukrainian context. The study sample included youth and adult internally displaced persons, veterans and their family members (wives and children), as well as community key informants and mental health professionals. We carried out free-list interviews, key informant interviews, and focus group discussions (FGDs) with a total of 226 participants. The qualitative study explored: participants’ perceptions of significant problems faced by internally displaced persons and veterans; descriptions of local functioning behaviors; and experiences with accessing, and delivering, mental health services.

Analysis allowed for the identification of psychosocial and mental health problems and symptoms of distress that were relevant to the study population. Both internally displaced persons and veterans described experiences of social isolation, difficulties with adaptation and (re-)integration, and conflicts with family members. Internally displaced persons also described missing home, fear, having a bad relationship with local residents/ lack of acceptance by the community, and conflicts in school among children. Veterans additionally named problems with substance use (alcohol and drug use), community members who are against them, feelings of being misunderstood by family members and the community, and aggression. For both groups, it was critical that mental health providers be trustworthy, accepting, and understanding of internally displaced persons and veterans’ status and experiences, as well as competent and effective.

### Study design

This study is conducted as a Hybrid Implementation-Effectiveness Type II [32] three-armed, single-blinded, randomized controlled trial in three cities in Ukraine. The study compares Brief CETA to Standard CETA and both Brief and Standard CETA to a wait-list control condition on our primary outcomes of depression, PTS symptoms, and daily functioning. A secondary aim is to evaluate implementation outcomes. The study design adheres to the Standard Protocol Items: Recommendations for Intervention Trials (SPIRIT) guidelines, including a SPIRIT Flow diagram, SPIRIT Schedule, and Checklist (Fig. 1 and Additional file 1).

**Fig. 1 Fig1:**
[figure not shown]
Standard Protocol Items: Recommendations for Interventional Trials (SPIRIT) Figure; schedule of enrollment, interventions, and assessments

### Participants and eligibility criteria

Recruitment for this trial began in March 2017 and is ongoing. The first participant was enrolled in the trial on 8 March 2017. Participants in this trial are adults living in or near three Ukrainian cities—Kyiv, Kharkiv, and Zaporizhia—who meet the following inclusion criteria:Adults aged 18 years or olderBeing either an internally displaced person from Eastern Ukraine (the Donbass or Crimea); a veteran of the Anti-Terrorist Operations (ATO) in Ukraine (including adult family members); a volunteer in the “revolution of dignity” in the war in Eastern Ukraine, or in support of internally displaced persons or veterans from these conflicts; or any other non-military person affected by the conflict in Eastern UkraineElevated depression and/or PTS symptoms as defined by:○ A score of 7 or above on the locally validated depression scale (possible score range: 0–24) or○ A score of 9 or above on the locally validated Post-Traumatic Stress Scale (possible score range: 0–39) or○ A score of 7 or above on the locally validated depression scale *and* 9 or above on the locally validated Post-Traumatic Stress ScaleEvidence of impaired daily functioning as assessed by a score of 4 or above on a locally validated scale of impaired functioning (possible score range: 0–32)Living in or around the three study cities for the duration of the study (at least 6 months) and able to regularly attend at least one of the locations where CETA is available

There are no restrictions on eligibility due to receiving other services. Participants who met the above criteria and who receive other health, mental health, social, behavioral, and any other type of services can be included.

Exclusion criteria include:An adult who is still a member of the armed forces (i.e., not a veteran)Acute suicidal or homicidal risk or active psychosis requiring immediate referral to psychiatric servicesSevere co-occurring medical problem that limits the ability to attend regular counseling sessions and/or requires immediate hospitalization

Assessors asked about suicide risk during the initial baseline assessment done on a tablet. If a possible participant responded “yes” to a single question about suicidal ideation in the past 2 weeks, they were asked four follow-up questions by the staff facilitating the baseline to gauge immediate risk. If someone answered positively to any of these follow-up questions, the assessor immediately called their supervisor, who provided clinical guidance by phone to assess for further risk, including past suicidal behavior. The supervisor was able to consult with clinical supervisors if they were unsure of the person’s level of risk. If the person was judged to be at immediate risk (i.e., past attempt and current ideation, a plan, and the means to carry out that plan) they were referred to a psychiatrist (who saw them within 24 hours), responded to by a local emergency psychiatric service, or driven directly to a hospital and were not randomized into a treatment condition. However, it was possible for a potential participant to be “cleared” by a psychiatrist and subsequently randomized into the trial. All clients were who were determined to have some risk, but not immediate risk, were asked to sign a safety contract and a safety plan was made to insure the person was checked on regularly and knew what to do and who to call if they started having suicidal thoughts. Any individual who could not respond to questions or presented with a severe illness was referred to a psychiatrist or physician and not included in the trial. Homicidal risk was not asked about explicitly, but if it came up during the baseline assessment or during any additional suicide safety procedures, the staff contacted a supervisor to create and sign a safety contract and made a referral to a psychiatrist to be seen within 24 hours.

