### Recruitment and baseline assessment

The participant flow is shown in Fig. 2. Both internally displaced persons and veterans are recruited through local service providers including government and non-governmental organizations (NGOs), through referral by study counselors from their existing client base, and through self-referral. Staff at the local NGOs were provided with a locally validated brief instrument that assessed symptoms of depression, anxiety, and PTS. This screening instrument is based on a previous validity study and Item Response Theory (IRT) analysis and includes the same symptom questions as the main study instrument, but does not ask about suicidal ideation or impaired functioning. As part of their regular services, the referring organizations use this instrument to assess their clientele for need of mental health services. When the instrument indicates depression and/or PTS symptoms, the person is informed about the study and asked if they agree to be contacted by a member of the study team.

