**Fig. 2 Fig2:**
[figure not shown]
Study protocol flow

Once a person has been identified as having elevated depression and/or PTS symptoms and agrees to be contacted, a study staff member sets a time to meet in person, complete consent procedures and conduct the baseline assessment to ensure trial eligibility. Both informed consent and the baseline assessment are self-administered on an electronic tablet. The study staff is present to facilitate the process, troubleshoot problems with the tablet and answer any questions, but will allow the potential participant to respond to questions in private. Consent is via a secure data collection/management software program (CommCare) [33] on a password-protected, handheld tablet. If the person does not consent to participate in the trial, the baseline assessment is not administered. If the person consents to the trial and completes the baseline, the person is immediately notified if they are eligible and whether they will receive treatment immediately or are asked to wait. If randomized to receive CETA, the participant is not told if they have been allocated to Brief or Standard CETA. Individuals who are not eligible for the study (either by not meeting the inclusion criteria or meeting one or more of the exclusion criteria) are thanked for their time and given a list of service organizations in their city.

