### Randomization, concealment, un-blinding

All eligible and consented adults are randomly allocated by a computer-generated randomization algorithm to either a wait-list control condition, the Brief CETA model, or the Standard CETA model. The unit of randomization is the individual. Block randomization is used to ensure equal distribution of treatment and control participants across providers. Within a provider, we randomly allocate 20 participants using a 1:2:2 (control:Brief:Standard) allocation ratio. Participants, counselors, study staff, and all clinical supervisors are blinded to study group allocation between Brief and Standard CETA conditions. This is done in an effort to ensure that all participants across both Brief and Standard CETA conditions will receive comparable treatment (see section “Concealment” below).

Study group allocation, either treatment or control only, is revealed to eligible participants immediately following the baseline assessment. If assigned to begin treatment right away, the study staff assigns a participant to a counselor based on availability and location of treatment. Counselors set up an initial meeting with the participant within 10 days of the baseline assessment. If assigned to control, the study staff set up a study assessment visit approximately 30 days after the completed baseline assessment.

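### Acute homicidal risk is an exclusion criterion, but no step before randomization systematically asks about it

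*Protocol article*

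**What the plan says.** The exclusion list under Participants and eligibility criteria puts acute suicidal risk, acute homicidal risk and active psychosis in one criterion, for cases that need immediate psychiatric referral.

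The same section then describes how risk is found. For suicide, a question on ideation in the past 2 weeks is part of the tablet baseline. If the answer is yes, "they were asked four follow-up questions by the staff facilitating the baseline to gauge immediate risk". People judged at immediate risk are sent to psychiatric care and "were not randomized into a treatment condition", although a psychiatrist may later clear them. For homicide: "Homicidal risk was not asked about explicitly, but if it came up during the baseline assessment" or in the course of further suicide safety procedures, staff contacted a supervisor, a safety contract was signed, and a psychiatrist was to see the person within 24 hours.

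Recruitment and baseline assessment describes the setting. "Both informed consent and the baseline assessment are self-administered on an electronic tablet", and staff attend but "will allow the potential participant to respond to questions in private". The person is told at once whether they are eligible and whether they start treatment or wait. The referral organizations' screening instrument, used before this, covers depression, anxiety and post-traumatic stress and "does not ask about suicidal ideation or impaired functioning".

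**The concern.** An exclusion for acute danger protects people only if the danger is looked for. Here two risks share one criterion. One is asked of everyone, and the other is acted on only if it happens to emerge. Someone with homicidal but not suicidal thoughts answers no to the ideation question, never reaches the suicide follow-up, and can complete the baseline without being asked.

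What is at stake is the safety of participants and third parties, and whether eligibility is applied evenly. The wait-list matters most. Under Control condition, the monthly contact is meant to pick up high-risk symptoms, but suicidality is the only one named. In the treatment arms, by contrast, Intervention fidelity says that session notes record yes/no answers on suicide and homicide risk, and the Safety element in Table 3 includes assessing homicide risk. The trial thus already uses a homicide question, but only after allocation and only for those receiving CETA, which is too late to support an exclusion.

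**Working it through.** The article gives no figure to reproduce. The check sets its statements side by side, with two short sums.

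**1. Is there any question before allocation?**

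| Step before allocation | Suicidal risk | Homicidal risk |
|---|---|---|
| Referral screen | Not asked | No item described |
| Tablet baseline, all candidates | 1 question | 0 questions (stated) |
| Staff follow-up | 4 questions, only after a yes on ideation | 0 questions; acted on if it comes up |

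The like-for-like comparison is the question put to everyone: 1 against 0. The four follow-up questions are conditional and should not be added to that count. Eligibility and treat-or-wait status are notified immediately after baseline, so no later step is described in which a question could be asked.

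**2. What happens to a case that does not come up?** Under Randomization, concealment, un-blinding, "All eligible and consented adults are randomly allocated". A person whose risk was not recognised looks eligible and enters the allocation.

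**3. Where does that person go?** With control:Brief:Standard at 1:2:2:
- wait-list share = 1 / (1 + 2 + 2) = 1/5 = 20%
- CETA share = (2 + 2) / 5 = 80%

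**4. When is the next contact?** The same section has CETA counselors set up a first meeting within 10 days of baseline. The first wait-list assessment is at about 30 days. The difference is at least about 30 − 10 = 20 days. After that, CETA participants meet a counselor whose notes record homicide-risk answers. Wait-list participants are seen monthly for about 6 months, with only suicidality named.

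**5. Whom can a change still reach?** Participants and eligibility criteria calls recruitment ongoing. Trial status expects it to end on 1 June 2018, and the article is dated 3 August 2018. If recruitment ended as expected, a baseline item reaches nobody new. A person wait-listed on the last day would wait until about 1 June + 6 months = early December 2018, so a monthly item could still help.

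**The case against.** The strongest reply is that this is a disclosed choice resting on clinical recognition. Staff are present at an in-person visit, some recruits come from service providers or counselors who may already know them, and a recognised risk leads to a supervisor, a safety contract and a psychiatrist within 24 hours. Active psychosis sits in the same criterion, and the article describes no item for it either. An exclusion need not have its own questionnaire item.

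Much of this stands, and it rules out several stronger readings that a reader might infer.
- *The exclusion is largely unapplied, or works only if the person volunteers the risk.* Not supported. The article says the risk was acted on if it came up, which can include what staff observe. The text supports not systematically asked, and no more.
- *A recognised homicidal case would be randomized anyway, because that sentence does not repeat the non-randomization rule.* Not supported. Acute homicidal risk is a listed exclusion, anyone "meeting one or more of the exclusion criteria" is treated as ineligible, and only eligible adults are allocated.
- *Suicide gets five questions and homicide none.* Four of the five follow only a yes, so this count inflates the contrast.
- *Wait-list participants are never asked.* This cannot be settled. The text names only suicidality, but the items in Table 2 are not shown.

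What does not stand is the suggestion that openness closes the gap. No reason is given for leaving the question out, and the trial treats homicide risk as something to ask about once treatment starts. Recognition is also a weak safeguard when the form is completed in private. That the item might be too late for baseline is a fair limit on the remedy, not an answer to the point.

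**Conclusion.** The concern holds in a limited form. Acute homicidal risk is an exclusion that the described procedure does not systematically ascertain before randomization, so following the plan as written can randomize a person it means to exclude. Of anyone missed, 1 in 5 would be expected on the wait-list, with about 30 days to the first study visit and monitoring text that names only suicidality.

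The article gives no frequency for missed cases; the number could be zero, and none is assumed here. The conclusion rests on the explicit statement that the question was not asked, and on no other step before allocation being described as asking it. The flow chart and Table 2 are not shown, but neither could overturn that statement about baseline. There is no claim about power, type I error or the treatment comparison. This is a safety and eligibility point that should be corrected because correcting it is cheap.

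**What to change.** Add one yes/no homicide-risk item to the baseline form, answered before allocation. Add the same item to the wait-list monthly form if it is not already there. A positive answer should trigger the supervisor call and psychiatrist referral that the article already describes. The question recorded in CETA session notes is a natural starting point, but its wording is not shown and should be checked for self-administered use.

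The cost is one tablet item, a few extra supervisor calls, and a short delay in allocation for those who answer yes. It will not detect people who deny the risk. The baseline item helps only people still to be enrolled; the monthly item helps those still waiting.
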